| **FDA** | Food and Drug Administration |
| **Fins** | fasting insulin |
| **GCP** | Good Clinical Practice |
| **HIPAA** | Health Insurance Portability and Accountability Act of 1996 |
| **HOMA2-IR** | homeostasis model assessment of insulin resistance |
| **ICF** | informed consent form |
| **ICH** | International Conference on Harmonisation |
| **IEC** | Independent Ethics Committee |
| **IGT** | impaired glucose tolerance |
| **IR** | insulin resistance |
| **IRB** | Institutional Review Board |
| **Lira** | liraglutide |
| **LSD** | Fisher’s Least Significant Difference |
| **OGTT** | oral glucose tolerance test |
| **PI** | Principal Investigator |
| **SAE** | serious adverse experience |
| **WHR** | waist-to-hip ratio |
| **2h-BG** | 2-hour blood glucose post-glucose load |

Protocol Synopsis

| **TITLE** | Association of serum Fetuin-B with insulin resistance and pre-diabetes in young Chinese women: evidence from a cross-sectional study and effect of liraglutide |
| --- | --- |
|  |  |
| **SPONSOR** | [name] |
|  |  |
| **FUNDING ORGANIZATION** | The National Natural Science Foundation of China (No. 81670755), the Natural Science Foundation of Chongqing (No.cstc2017jcyjAX0050) |
| **NUMBER OF SITES** | +86, +023 |
|  |  |
| **RATIONALE** | Fetuin-B has been reported to be involved in glucose and lipid metabolism and associated with the occurrence of diabetes. The main purpose of this study is to explore the changes of circulating Fetuin-B in young women with pre-diabetes and to analyze the relationship between Fetuin-B and the occurrence and development of IR.. |
|  |  |
| **STUDY DESIGN** | This is a cross-sectional study. |
|  |  |
| **PRIMARY OBJECTIVE** | Explore the changes of circulating Fetuin-B in young women with pre-diabetes and to analyze the relationship between Fetuin-B and the occurrence and development of IR |
|  |  |
| **SECONDARY OBJECTIVES** | Explore the effects of liraglutide (Lira) on Fetuin-B and obesity. |
|  |  |
| **NUMBER OF SUBJECTS** | 304 |
|  |  |
| **SUBJECT SELECTION**  **CRITERIA** | Inclusion Criteria:  IGT was diagnosed according to the American Diabetes Association (ADA)(American Diabetes 2012). The presence of pre-diabetes was defined by the occurrence of IGT at 2h-OGTT. M-value < 6.28 was considered to have IR.  Lira: included age of 18-35 and BMI of 25-35 kg/m2  Exclusion Criteria:  type 1 diabetes mellitus (T1DM), T2DM, hypertension, and other important organ diseases such as heart, liver, and kidney  Lira: included the family history of thyroid tumor, the history of medullary thyroid carcinoma, severe gastrointestinal disease, acute pancreatitis, and pregnancy. |
|  |  |
| **TEST PRODUCT, DOSE, AND ROUTE OF ADMINISTRATION** | Product Lira at 1.8mg dose  Liar was injected subcutaneously once a day. The dose increased from 0.6 mg to 1.8 mg |
|  |  |
|  |  |
| dURATION OF SUBJECT PARTICIPATION AND DURATION OF STUDY | Subjects will be on study for up to 24 weeks  **Screening :**  2 weeks  **Treatment:** 24 weeks  **Follow-up:** 24 weeks  The total duration of the study is expected to be 24weeks. |
| **E** |  |
| **CONCOMMITANT MEDICATIONS** | No |
|  |  |
| **Efficacy Evaluations** | Physical examination and biochemical tests, OGTT, and EHC tests were performed before treatment, 12 and 24 weeks after treatment. |
| ***Primary endpoint*** | - 24 weeks after application of lira |
| ***Secondary endpoints*** | - Serious adverse events within 24 weeks |
| **Other Evaluations** | BMI, Fat %, WC, TG, FBG, FIns, HbA1c and HOMA2-IR |
| **Safety Evaluations** | Change in clinical safety labs from baseline to 24weeks  Incidence of adverse events is 0% |
| **Planned Interim Analyses** | When approximately 50% of patients have completed the study through outpatient department of Endocrinology, an interim analysis for safety will be conducted by an independent data monitoring committee. Serious adverse events will be monitored by the committee on an ongoing basis throughout the study. |
|  |  |
| **STATISTICS**  **Primary Analysis Plan** | SPSS version 24.0 software was used for statistical analysis. Data were expressed as mean±SD or median. Variables that are not normally distributed were converted logarithmically. Analysis of variance was used for comparison among groups, and LSD test was used for comparison between two groups. The relationship between serum Fetuin-B and other variables was evaluated by linear regression analysis with controlled covariates. Multiple linear regression analysis was used to identify independent factors associated with serum Fetuin-B. Multiple logistic regression analysis was conducted to understand the association of serum Fetuin-B with IR and IGT. Cochran-Armitage trend test and Row Mean Scores analysis were performed to investigate the changing trend of the Fetuin-B level in IGT and IR-NG groups. ROC curves were constructed to evaluate the sensitivity and specificity of serum Fetuin-B in predicting IR and IGT |
| **Rationale for Number of Subjects** | A total of 304 young women were enrolled in this study, including 80 newly diagnosed IR patients (IR-NG group), 97 individuals with impaired glucose tolerance (IGT group), and 127 healthy women (NGT group). The sample size is sufficient, the distribution of each group is even and appropriate, the setting of lira subgroups is reasonable, which make the results convincing. |

# BACKGROUND

T2DM has been considered a chronic disease related to the elderly, but with rapid economic and social development in recent years, changes in lifestyle and diet structure have resulted in increasing rates of T2DM and obesity in adolescents. Serum Fetuin-B is considered to be an adipo-hepatokine and a member of the cystatin superfamily of cysteine protease inhibitors, and serum Fetuin-B levels are significantly related to IR. Therefore, the relationship between serum Fetuin-B and IR is still controversial.

## Overview of Non-Clinical Studies

The results from Meex et al. showed that Fetuin-B could induce IGT by inhibiting the effect of insulin on myotubes and hepatocytes in mice. In obese mice, knockout of the Fetuin-B gene significantly improved impaired glucose tolerance (IGT). In an in vivo study, it was shown that Fetuin-B may regulate blood glucose through a non-insulin signaling pathway, but the specific mechanism is still unclear.

## Overview of Clinical Studies

In a clinical study, Qu et al. found that the serum Fetuin-B levels in T2DM patients were significantly higher than those in IGT and normal subjects, and serum Fetuin-B was correlated with TG, fasting insulin, homeostasis model assessment of insulin resistance (HOMA-IR), and insulin secretion in the first phase. In addition, it has been reported that serum Fetuin-B levels are significantly increased in patients with nonalcoholic fatty liver disease (NAFLD), and related to IR. In contrast, a recent study showed that the mRNA expression of Fetuin-B in the liver was not associated with HOMA-IR. For more detail refer to the Investigator’s Brochure.

# STUDY RATIONALE

There have been some reports that Fetuin-B is related to metabolic diseases in recent years. However, most of the previous studies were cross-sectional and descriptive studies. They were merely a preliminary exploration of Fetuin-B, and there was no intervention experiment to fully prove the relationship between Fetuin-B and human IR, and no state-of-the-art methodology was used. In addition, there have been many confounding factors in previous studies, such as middle-aged and elderly subjects, most of whom had long-term dyslipidemia or other metabolic diseases, and with a long history of drug treatment. In addition, age and gender also have important effects on obesity and IR. Therefore, if applied to clinical work, the previous results have some limitations.

# STUDY OBJECTIVES

## Primary Objective

The primary objective is to assess the association of serum Fetuin-B with IR-NG and IGT.

## Secondary Objectives

The secondary objective is to assess the clinical efficacy as measured by the change in physical examination and biochemical tests, OGTT, and EHC tests before treatment, 12 and 24 weeks after treatment.

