# Criteria for evaluation

## Primary Efficacy Endpoint

24 week after application of lira (It has been well known that Lira is generally used at doses up to 1.8 mg as an anti-diabetic agent, but higher doses (up to 3.0 mg) and long terms have been approved for weight loss in the US and Europe in obese individuals, irrespective of hyperglycemia. Given the weight characteristics of the Chinese population, we treated IR patients with 1.8 mg Lira for 24 weeks).

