### Physical Examination

After fasting for 10-12 h, all subjects were given a physical examination and biochemical tests by professionals. The physical examination included body weight, blood pressure (BP), waist circumference (WC), and body fat content (Fat %). A complete physical examination will be performed by either the investigator or a subinvestigator who is a physician before treatment. Qualified staff (MD, NP, RN, and PA) may complete the abbreviated physical exam at all other visits. New abnormal physical exam findings must be documented and will be followed by a physician or other qualified staff at the next scheduled visit.

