## Analysis of Primary Endpoint

After application of lira, Physical examination and biochemical tests, OGTT, and EHC tests were performed before treatment, 12 and 24 weeks after treatment.

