## Interim Analysis

All of the subjects were asked to come back to the outpatient to receive physical examination and biochemical tests, OGTT, and EHC tests at 12 week to assess the effect of lira.

The sample size for this protocol was determined by the patients number of the Second Affiliated Hospital of Chongqing Medical University from January 2017 to December 2019. We planed to enroll 300 subjects for cross-sectional study and 30 subjects for lira administration.

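### The primary efficacy endpoint for liraglutide names week 24 but no variable, and efficacy is judged on about 15 or more unranked measures at two visits

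*Protocol*

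**What the plan says.** Five parts of the protocol bear on how liraglutide is judged.

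- **Synopsis, secondary objectives:** "Explore the effects of liraglutide (Lira) on Fetuin-B and obesity". Under other evaluations the synopsis also lists, without ranking, "BMI, Fat %, WC, TG, FBG, FIns, HbA1c and HOMA2-IR".
- **Section 3.2:** clinical efficacy is taken to be "the change in physical examination and biochemical tests, OGTT, and EHC tests before treatment, 12 and 24 weeks after treatment".
- **Section 5.1 (and the synopsis primary endpoint):** "24 week after application of lira", followed by a rationale for dose and duration. No measure is attached to the time point.
- **Section 15.3, Analysis of Primary Endpoint:** "Physical examination and biochemical tests, OGTT, and EHC tests were performed before treatment, 12 and 24 weeks after treatment". This is a schedule; it names no variable, contrast or test.
- **Section 15.5, Interim Analysis:** all subjects return for the same examinations, including "OGTT, and EHC tests at 12 week to assess the effect of lira".

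No significance level is stated. The synopsis names LSD for comparing two groups but no test for change within the treated women. Section 15 promises a separate SAP, which is not shown.

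**The concern.** Nothing in the protocol says which variable decides whether liraglutide worked. The synopsis points to Fetuin-B and obesity. Section 3.2 widens this to four test panels at two visits and replaces exploring with assessing clinical efficacy. The two sections that should settle the matter, 5.1 and 15.3, give a time and a schedule.

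Fetuin-B is the study's own question. As written, a null result on Fetuin-B could be reported beside a chance change in a lipid or a 12-week insulin value, and the protocol would give the reader no basis for weighting one above the other. Section 2 criticises earlier work for lacking an intervention experiment, so the liraglutide part is likely to be read as more than description.

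**Working it through.** The protocol gives no error rate, power or effect size for this part, so there is no stated figure to reproduce.

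**Step 1: count the variables.**
- Physical examination: body weight, blood pressure, waist circumference, body fat = 4.
- Biochemical parameters, also listed at Visits 2 and 3: 10.
- Clamp: M-value = 1.
- Minimum: 4 + 10 + 1 = 15 variables, and 15 × 2 visits = 30 comparisons.
- Adding serum Fetuin-B gives 16. HOMA2-IR and the intermediate OGTT samples would add more.
- A narrow count takes the eight synopsis variables plus Fetuin-B and M-value: 8 + 2 = 10.

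**Step 2: independent tests.** Assume two-sided 0.05 per test and no true effect on anything. The chance of at least one false positive in k tests is 1 − 0.95^k.
- One variable at two visits: 1 − 0.95² = 0.098.
- Ten variables at one visit: 1 − 0.95^10 = 0.40.
- Sixteen variables at one visit: 1 − 0.95^16 = 0.56.
- Thirty comparisons: 1 − 0.95^30 = 0.785.

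**Step 3: allow for correlation.** These figures come from simulated one-sample t tests on change scores. They use n = 26 (the treated number in Section 8.1; Section 15 planned 30), an assumed correlation of 0.5 between the 12- and 24-week changes, and an assumed common correlation between variables. Repeat runs differ by 0.01 to 0.02.

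| Variables | Correlation between variables | Both visits | Week 24 only |
| --- | --- | --- | --- |
| 10 | 0 | 0.62 | 0.40 |
| 10 | 0.5 | 0.47 | 0.29 |
| 10 | 0.8 | 0.30 | 0.17 |
| 16 | 0 | 0.78 | 0.56 |
| 16 | 0.5 | 0.59 | 0.38 |
| 16 | 0.8 | 0.36 | 0.22 |

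**Step 4: does the sample size matter?** With 15 variables at two visits, n = 26 gives 0.68 and 0.58 at between-variable correlations 0.3 and 0.5. With n = 300 the figures are 0.69 and 0.58. The risk does not depend on n.

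**Step 5: what one key test offers.** A single paired test at 0.05 keeps the false-positive chance at 0.05. With 26 women it has 80% power for a mean change of about 0.57 SD. Bonferroni over 30 comparisons (0.05/30 = 0.00167 each) would need about 0.87 SD.

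**Step 6: is the key measurement scheduled?** Sections 3.2 and 15.3 and the Vital Signs paragraph place OGTT and clamp at 12 and 24 weeks, and the OGTT section draws Fetuin-B during the OGTT. The lists for Visits 2 and 3 name the ten blood tests but not Fetuin-B, OGTT or EHC, and end with an unfilled item for additional procedures. Appendix 1 marks all three at Visit 1 only.

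**The case against.** Several objections have force.

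- **Some ordering and an exploratory word exist.** A reader might infer that nothing is ranked or labelled. The documents do not support that. Week 24 is named for the primary efficacy endpoint, week 12 sits under Interim Analysis, liraglutide is the secondary objective, and the synopsis says it will explore. This stands. But it orders the visits and not the variables, and the synopsis uses the same verb for the primary objective, so the word does not set the liraglutide part apart.
- **Multiplicity belongs in the SAP.** An adjustment method may properly sit there, so its absence here is not the point. The objective and the endpoint variable are protocol content, and Sections 3.2, 5.1 and 15.3 state them in a form that selects nothing.
- **There is no rule that any one change counts as success.** Correct: Section 3.2 lists measurements and sets no criterion. The rates describe what could happen if every variable were tested at 0.05. They are not the error rate of a stated decision rule.
- **A chance finding is not necessarily likely.** It is tempting to say that one is probable, or that 26 women make it so. The first depends on an unstated alpha and on correlation; many scenarios fall below one half. The second is wrong, as Step 4 shows.
- **Liraglutide is expected to act on weight and glucose.** Section 5.1 describes it as an anti-diabetic agent also approved for weight loss, so a null on every marker is a reference case and not a forecast.

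**Conclusion.** The concern holds in this form: the primary efficacy endpoint has a time but no variable, its analysis section only repeats the battery, and Section 3.2 spreads clinical efficacy over about 15 or more unranked variables at two visits in firmer language than the synopsis uses. If every variable were tested, the chance of at least one false positive would be several times a nominal 0.05. Fixing attention on week 24 lowers that chance but does not remove it; only naming a variable does. The figures assume two-sided 0.05 per test, no true effect on any variable, between-variable correlation from 0.8 down to 0, and correlation 0.5 between visits. The count of post-baseline variables also depends on resolving the scheduling contradiction.

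**What to change.** - In the synopsis and Sections 3.2, 5.1 and 15.3, name change in fasting serum Fetuin-B from baseline to week 24 as the single key liraglutide outcome.
- Label all other variables, including BMI and the other obesity measures, and every 12-week comparison as exploratory. Report them as mean change with 95% confidence intervals.
- In Section 3.2, use the synopsis verb (explore) in place of assessing clinical efficacy.
- Reconcile the lists for Visits 2 and 3 and Appendix 1 with Sections 3.2 and 15.3 and the Vital Signs paragraph, so that the week-24 Fetuin-B measurement exists.
- Optionally, test change in BMI at week 24 only if the Fetuin-B test is significant, following the order in the synopsis objective.

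The cost is mostly wording, but the visit schedule must be corrected as well. The price in claims is that changes in other markers, and any change at week 12, can be described but not presented as demonstrated effects.

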# STUDY DESIGN

## Study Overview

This is a cross-sectional study. 304 of subjects are enrolled and applied with biochemical tests, OGTT, and EHC tests on admission. In the subgroup, each subject will be administered lira at the dose of 1.8mg, once a day, and evaluations will be taken before treatment, 12 and 24 weeks after treatment.

Screening data will be reviewed to determine subject eligibility. Subjects who meet all inclusion criteria and none of the exclusion criteria will be entered into the study.

The following treatment regimens will be used:

- Experimental treatment Lira at the following doses: increased from 0.6 mg to 1.8 mg

Total duration of the study is expected to be 24 weeks.

# Criteria for evaluation

## Primary Efficacy Endpoint

24 week after application of lira (It has been well known that Lira is generally used at doses up to 1.8 mg as an anti-diabetic agent, but higher doses (up to 3.0 mg) and long terms have been approved for weight loss in the US and Europe in obese individuals, irrespective of hyperglycemia. Given the weight characteristics of the Chinese population, we treated IR patients with 1.8 mg Lira for 24 weeks).

## Secondary Efficacy Endpoints

- Serious adverse events within 24 weeks.

## Safety Evaluations

- The basic indicators of the patient are all in the normal range.
- Incidence of adverse events is 0%.

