### Adverse Events

Information regarding occurrence of adverse events will be captured throughout the study. Duration (start and stop dates and times), severity/grade, outcome, treatment and relation to study drug will be recorded on the case report form.

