## Visit 2 (12 weeks)

1. Record any Adverse Experiences and/or Review subject diary for adverse experiences and dosing compliance.
2. Concomitant medications review.
3. Perform abbreviated physical examination.
4. Perform and record vital signs.
5. Collect blood for clinical laboratory tests (TC, TG, HDL-C, LDL-C, FFA, HbA1c, FBG, 2h-BG, FIns, 2h- INS).
6. List all additional procedures.

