# ADVERSE Experience REPORTING AND DOCUMENTATION

## Adverse Events

An adverse event (AE) is any untoward medical occurrence in a clinical investigation of a patient administered a pharmaceutical product and that does not necessarily have a causal relationship with the treatment. An AE is therefore any unfavorable and unintended sign (including an abnormal laboratory finding), symptom or disease temporally associated with the administration of an investigational product, whether or not related to that investigational product. An unexpected AE is one of a type not identified in nature, severity, or frequency in the current Investigator’s Brochure or of greater severity or frequency than expected based on the information in the Investigator’s Brochure.

The Investigator will probe, via discussion with the subject, for the occurrence of AEs during each subject visit and record the information in the site’s source documents. Adverse events will be recorded in the patient CRF. Adverse events will be described by duration (start and stop dates and times), severity, outcome, treatment and relation to study drug, or if unrelated, the cause.

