APPENDIX 1. Schedule of Study Visits

|  | **Visit 1 (Day/Week/Month #)a** | **Visit 2 (Day/Week/Month #)a** | **Visit 3 (Day/Week/Month #)a** |
| --- | --- | --- | --- |
| Informed Consent | **x** |  |  |
| Medical History | **x** |  |  |
| Complete Physical Exam | **x** |  |  |
| Abbreviated Physical Exam |  | **x** | **x** |
| Height | **x** | **X** | **X** |
| Weight | **x** | **x** | **x** |
| WC |  |  |  |
| FAT% |  |  |  |
| Vital Signs | **x** | **x** | **x** |
| Pharmacokinetics |  | **x** |  |
| Serum Fetuin-B | **x** |  |  |
| Pregnancy Test (Urine or Serum) | **x** |  |  |
| Hematology | **x** |  |  |
| OGTT | **x** |  |  |
| EHC | **x** |  |  |
| Urinalysis | **x** |  |  |
| Dispensing or Administration of Study Drug | **X** | **X** | **X** |
| Counting of Returned Study Drug |  | **X** | **X** |
| Concomitant Medication Review | **X** | **X** | **X** |
| Adverse Experiences |  |  |  |

a 2 days

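### Adverse-event incidence is written as a preset result of 0% instead of a measure, and the visit schedule contradicts the text on adverse-event recording and leaves haematology and urinalysis without a follow-up value

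*Protocol*

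**What the plan says.** Section 5.3 (Safety Evaluations) has two items. The first is "The basic indicators of the patient are all in the normal range"; the second is "Incidence of adverse events is 0" per cent. The synopsis repeats the second but not the first. In its place the synopsis lists "Change in clinical safety labs from baseline to 24weeks".

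On collection, Section 9.1 states: "Information regarding occurrence of adverse events will be captured throughout the study". The Visit 2 list (Section 10.2) instructs the site to "Record any Adverse Experiences and/or Review subject diary for adverse experiences and dosing compliance", and Visit 3 (Section 10.3) has the same instruction. Section 11.1 has the investigator probe "for the occurrence of AEs during each subject visit and record the information in the site’s source documents". Section 11.2 collects serious events from consent until the procedures of the final visit are done.

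Appendix 1 has a row labelled "Adverse Experiences" with no tick under any of the three visits. It ticks haematology and urinalysis at Visit 1 and nowhere else.

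On duration, the synopsis gives 2 weeks of screening, 24 of treatment and 24 of follow-up, and then: "The total duration of the study is expected to be 24weeks".

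**The concern.** A safety evaluation should say what is counted, in whom and over what period. Section 5.3 gives the answer instead. Taken literally, a single adverse event would put the trial at odds with its own protocol, and a trial that recorded none would appear to confirm a value fixed beforehand, with no statement of uncertainty. In a treated group of 26 to 30 women that uncertainty is large.

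The schedule adds a practical risk. Sites often work from the visit table, and this one shows no adverse-event task at any visit. If events are recorded less completely for that reason, the count moves towards the 0% already written down. The laboratory part of the safety evaluation is also only partly deliverable as scheduled.

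**Working it through.** **The stated figure.** The 0% comes with no event count, denominator or assumed rate, so there is nothing to reproduce. Section 15.4 says only that safety data will be summarised by treatment group. Section 8.1 describes one treated group, so that sentence does not supply the missing measure.

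**What an observed zero would mean.** Inputs: 26 treated women (Section 8.1) and 30 planned (the sample-size text under Section 15.5). The 95% level is my assumption, since the protocol gives none for safety. With 0 events in n, the exact (Clopper-Pearson) upper limit is 1 − 0.025^(1/n) two-sided and 1 − 0.05^(1/n) one-sided.

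- n = 26: 1 − 0.025^(1/26) = 13.2%; 1 − 0.05^(1/26) = 10.9%.
- n = 30: 1 − 0.025^(1/30) = 11.6%; 1 − 0.05^(1/30) = 9.5%.

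The chance of seeing no event at true incidence p is (1 − p)^n. The protocol gives no p, so a range is shown:

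| Assumed p | n = 26 | n = 30 |
| --- | --- | --- |
| 5% | 26% | 21% |
| 10% | 6.5% | 4.2% |
| 20% | 0.3% | 0.1% |

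An event affecting 1 woman in 20 would go unseen in about a quarter of trials of 26 women (0.95^26 = 0.264).

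**Adverse-event recording, text against schedule.**

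| Visit | Text | Appendix 1 row |
| --- | --- | --- |
| 1 (week 0) | Not in the Section 10.1 list; Section 11.1 covers every visit | blank |
| 2 (week 12) | Required (Sections 10.2, 11.1) | blank |
| 3 (week 24) | Required (Sections 10.3, 11.1) | blank |

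The conflict is plain at Visits 2 and 3. At Visit 1 the blank agrees with Section 10.1 but not with Section 11.1.

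**Laboratory follow-up.** The blood lists at weeks 0, 12 and 24 (Sections 10.1 to 10.3) are identical: lipids, free fatty acids, HbA1c, glucose and insulin. Change to week 24 is computable for these. Haematology and urinalysis appear only in Appendix 1, at Visit 1, and no text in Section 9 or 10 adds a later sample. Their change to week 24 is not computable. The synopsis does not say which tests its safety laboratory evaluation covers.

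**Duration.** Screening plus treatment is 2 + 24 = 26 weeks, against a stated total of 24.

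**The case against.** The strongest reply is that adverse events will be collected whatever Section 5.3 says. Section 9.1 records duration, severity, outcome and relation to drug. Visits 2 and 3 and the early withdrawal visit all include recording. Section 11 defines severity grading, causality and seriousness, and Section 5.2 already names serious adverse events within 24 weeks as an endpoint. Appendix 1 also looks unfinished: its waist-circumference and body-fat rows are blank too, and its column headings are unfilled template text. Interval methods are normally left to the SAP, and the binomial figures reflect a small group that no rewording enlarges. The primary objective (Section 3.1), the cross-sectional Fetuin-B association, is untouched.

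Most of this stands, and it limits the point. A reader might infer that the trial cannot yield a sound safety estimate; the collection provisions just listed do not support that. A reader might also add 2 + 24 + 24 to get 50 weeks and conclude that the adverse-event window is open. That sum assumes follow-up comes after treatment. No visit is scheduled after week 24, serious events are collected to the final visit, and Section 5.2 counts them within 24 weeks, so the documents point to a window ending at week 24. Finally, a reader might say that the all-normal line contradicts eligibility, which rests on abnormal 2-hour glucose or M-value. The basic indicators are not defined, so that is vagueness and not a demonstrated contradiction.

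The reply does not remove the core. The protocol does not leave a safety measure to the SAP; it puts a result where the measure belongs. An unfinished table that disagrees with the text still has to be reconciled.

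**Conclusion.** Wrong as written, in a limited form. Three defects hold on the face of the protocol: the 0% line in Section 5.3 and the synopsis, with the all-normal line in Section 5.3 only; the blank adverse-event row against Sections 9.1, 10.2, 10.3 and 11.1; and haematology and urinalysis with no follow-up value, despite a promised change in safety laboratory values to week 24. The third covers those two tests only, because the metabolic panel is drawn at weeks 0, 12 and 24. How far it undercuts the promise depends on what the sponsor meant by safety laboratory tests.

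The binomial figures show why an observed zero would not mean absence of risk. They rest on the assumed 95% level and on either 26 or 30 treated women, and they do not measure any bias. The 26-against-24-week mismatch is minor.

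**What to change.** 1. In Section 5.3 and the synopsis, replace the 0% line with the number and percentage of treated women with at least one adverse event and with at least one serious adverse event, each with an exact 95% interval. Delete the all-normal line from Section 5.3.
2. Complete the adverse-event row of Appendix 1 to agree with Sections 9 to 11, and settle Visit 1, where Sections 10.1 and 11.1 differ.
3. State which tests the synopsis's safety laboratory evaluation covers, and reconcile that list with the samples scheduled at follow-up. The choice of tests is the sponsor's; the passages only have to agree.
4. As a minor correction, reconcile the screening, treatment, follow-up and total-duration statements in the synopsis.

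The cost is wording and table corrections. The reported safety statement will be less favourable than 0%: even with no events, it would carry an upper limit above 10%.
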